## Abstract

Pre-eclampsia (PE), a pregnancy-specific hypertensive disorder, characterized by the development of placental endothelial dysfunction, remains a major source of maternal and perinatal morbidity and mortality, especially in low- and middle-income settings. Periodontal disorders during pregnancy, and particularly periodontal pathogens, may be related to the risk of PE. Standard oral hygiene methods, based mainly on the joint use of toothbrushes and interdental brushes, reduce periodontal inflammatory risk and modulate the dysbiosis of the oral microbiome. The aim of this trial is to compare the PE outcomes in high-risk pregnant women receiving oral prophylactic measures to a control group. This trial is designed as a two-arm, parallel, cluster randomized controlled trial with the antenatal obstetric clinic as the unit of randomization and an allocation ratio of 1:1. The pregnant women will be included at 3 months of pregnancy and will be followed throughout the pregnancy. The primary outcome measure will be the incidence of PE from a baseline during the pregnancy. Secondary outcomes measures will include changes from the baseline in quantification of the pathogenic bacterial load of the interdental microbiota, the severity scores of periodontal indicators, and the incidence of adverse perinatal outcomes. This trial should demonstrate that the implementation of daily oral hygiene reduces oral dysbiosis, the incidence of periodontal disease, and the risk of PE.

## 1. Introduction

Pre-eclampsia (PE) remains a major source of maternal and perinatal morbidity and mortality, especially in low- and middle-income settings [1]. PE is a pregnancy-specific hypertensive disorder that is characterized by the development of placental endothelial dysfunction resulting in, among the most common diagnostic features, concomitant hypertension and proteinuria that may evolve into organs with fluctuating clinical specificities [2,3]. Obesity, chronic hypertension, metabolic or cardiovascular risks, and severe anemia, predisposing to endothelial dysfunction as part of an excessive systemic inflammatory response, have been found to be the highest risk factors of PE [4,5,6]. However, the prediction and prevention of PE is not possible, as the multifactorial pathogenesis of the different types of PE is not clearly identified [7]. The analysis of the alteration of placental microbiome is a possible therapeutic approach in the prevention and management of PE [8]. As an early signal of a future increase in cardiovascular and metabolic diseases, PE may warrant both educational and lifestyle interventions to improve perinatal outcomes [9,10].

In recent decades, numerous studies have shown that periodontal disease (PD) has contributed to prematurity and low birth weight [11,12,13]. PD is a chronic, multifactorial, non-communicable disease and inflammatory disease of polymicrobial origin resulting from an increase in pathobionts in the microbiota [14]. Maternal periodontopathogens may be linked to placental damage and premature pathogenesis [15], as well as the association between the presence of pathogenic oral bacteria in the placenta and adverse pregnancy outcomes [16]. PD may lead to systemic complications including pregnancy complications [17]. Current studies indicate that periodontal disorders during pregnancy, and particularly periodontal pathogens, may be related to the risk of PE [18]. Conversely, there is limited emerging evidence that pregnancy infers dysbiosis in the maternal oral microbiome [19].

Standard oral hygiene methods, based mainly on the joint use of toothbrushes and interdental brushes, reduce periodontal inflammatory risk and modulate the dysbiosis of the oral microbiome [20,21,22]. Individual oral prophylaxis could impact bloodstream entry of periodontal pathogenic bacteria such as *Porphyromonas gingivalis*, whose action on the placental endothelium is scientifically validated [23]. This periodontal pathogen is the most common microorganism present during bacteremia in patients with periodontitis [24,25], with the capacity to cause inflammation even if present in insignificant quantities [26]. It is also the most common microorganism in the amniotic fluid and placental tissue associated with adverse pregnancy outcome [27,28].

The purpose of this trial is to compare the PE outcomes in high-risk pregnant women receiving oral prophylactic measures to a control group. One specific question is addressed as follows according to the PICO principles: In high-risk pregnant women (Population), do oral prophylactic measures (Intervention) have a beneficial effect on PE parameters (Outcome) compared to pregnant women without any specific oral prophylactic measures (Control)?

## 2. Material and Methods

### 2.1. Trial Design

This study protocol is reported according to the Standard Protocol Items: Recommendations for Interventional Trials (SPIRIT) guidelines [29]. This trial is designed as a two-arm, parallel, cluster randomized controlled trial with antenatal obstetric clinic as the unit of randomization and an allocation ratio of 1:1 (Figure 1). 

### 2.2. Study Setting

This study will be conducted within the establishments of the National Hospital Center of Dakar, Senegal, and of Ouagadougou, Burkina Faso.

### 2.3. Study Population

#### 2.3.1. Eligibility Criteria

The obstetrics clinics of the institutions (clusters) will be selected under the general principle that the attending population in each country should be similar with regard to socio-demographic factors of participants planning to deliver in hospitals. Criteria for clinic selection will be: (i) clinics in the public system, (ii) Each clinic’s ability to include at least 150 new pregnant women over a period of no more than 6 months, (iii) access to clinic is the reference site for all high-risk women for PE, and (iv) intervention and control clinics will be in the same geographical area but serving distinct neighborhoods.

The individual eligibility criteria will be: (i) pregnant woman, (ii) women from sub-Saharan Africa, (iii) aged from 18 to 35 years old, (iv) nulliparous at the time of the obstetrical consultation, (v) up to 12 weeks pregnant, (vi) acceptance of the terms and conditions of the study, and (viii) signature of the informed consent form.

#### 2.3.2. Exclusion Criteria

The exclusion criteria will be pregnant women with: (i) fetal distress, (ii) congenital uterine and vaginal abnormalities, (iii) infectious or systemic diseases such as HIV, tuberculosis, candidiasis, cancers, hemopathies, (iii) premature termination of pregnancy for medical reasons, (iv) periodontal lesions of stage II, III, IV (i.e., PD ≥ 4 mm, and/or CAL ≥ 4 mm), generalized (>30% of sites), (v) history or treatment of PD, (vi) a course of dental or orthodontic treatment, (vii) absence of the 4 premolar–molar pairs, (viii) less than 20 natural teeth, excluding third molars, (ix) medication affecting the gum and/or oral mucosa, (x) regularly using interdental brushes and/or dental floss and/or mouthwash, and (xi) unable to answer questions or non-cooperative.

### 2.4. Interventions

The intervention will be the implementation, or not, of oral prophylactic techniques. The control group will continue its usual oral hygiene practice. For the study group, the oral prophylactic intervention will consist of provision of specific package including soft-bristled manual toothbrush, toothpaste, and a kit of calibrated interdental brushes (IDBs) (Curaprox CPS; Curaden) of sizes corresponding to the diameter of their interdental spaces. The participants will be instructed to brush their teeth twice-daily and to realize daily interdental brushing until delivery. The instructions for the use of the toothbrush and IDBs comprised verbal instructions supported by practical demonstration. The first use of the material will be conducted under the supervision of a qualified public health professor.

Our research is a pragmatic study that does not want to interfere with the organization of care provided during obstetrical visits. In the public health systems, except for very punctual dental emergencies, no periodontal care is suggested or provided. 

### 2.5. Outcomes

#### 2.5.1. Primary Outcome Measures

Primary outcome measure will be the incidence of PE from baseline during the pregnancy. PE is defined as diastolic pressure >90 mm Hg after two 4 h intervals or >110 mm Hg once; systolic pressure >140 mm Hg after two 4 h intervals or >160 mm Hg once, after 20 weeks of gestation in combination with proteinuria 2+ or more; >300 mg/24 h, >500 mg/L, or urinary protein/creatinine ratio >0.034 g/mmol.

#### 2.5.2. Secondary Outcome Measures

Secondary outcomes measures will include changes from baseline in:-Quantification of the pathogenic bacterial load of the interdental microbiota.-Severity scores of periodontal indicators: pocket probing depth (PPD), clinical attachment level (CAL), gingival index (GI), plaque index (PI), bleeding on interdental brushing index (BOIB).-Incidence of adverse perinatal outcomes (low birth weight and preterm delivery).

### 2.6. Participant Timeline

The schedule of visits will overlap with the recommended follow-up schedule for pregnant women. The participation timeline of the trial is presented in the Table 1.

#### 2.6.1. Pre-Screening and Assessment for Eligibility

Participants will be screened at their first prenatal visit. If they meet the eligibility criteria, the study will be presented to them. If they agree to participate and consent to be screened, the inclusion visit will be scheduled at 3 months of pregnancy.

#### 2.6.2. Inclusion, Prenatal Examination, Oral Examination, and Baseline Interdental Microbiota Sampling (T1)

Participants will sign the informed consent form. A clinical obstetric and oral examination, followed by interdental microbiota sampling, will be performed for all participants.

Prenatal clinical examination

The obstetric clinical examination will include the measurement of weight, height, blood pressure, and the uterine height of the participants.

Biological analysis

The biological analysis will determine the level of red blood cells, white blood cells, neutrophils, C-reactive protein, creatinine, blood sugar, uremia, and proteinuria.

Oral clinical examination and sampling of the interdental microbiota

Two calibrated periodontists per site, properly trained before the beginning of the study, and who will be blinded regarding the group category at the time of the evaluation, will perform the periodontal assessment of all patients. Calibration of examiners will include a group of 32 experienced dentists. Intraclass correlation coefficients for PD and CAL will be calculated at the site level. The intra- and inter-examiner coefficients for CAL will range between 0.80 and 0.85, and between 0.75 and 0.85 for PD, respectively.

For all participants, the same four interdental sites (15–16, 25–26, 35–36, and 45–46) will be assessed; the interdental spaces between molars and premolars are the most susceptible to gingival inflammation [30,31]. The interdental diameter will be determined using a graduated conical probe—the CURAPROX IAP calibration probe (Curaden, Kriens, Switzerland) [32]. The working portion includes colored bands from the tip to the base corresponding to IDBs by increasing diameter. The largest section of each colored band corresponds to the cleaning efficiency diameter of the respective brush. This will make it possible to select the calibrated IDB (Curaden) appropriate to the diameter of the interdental space. Each previously selected tooth will be isolated using sterile cotton rolls, and the interdental biofilm will be removed using this sterile IDB. For each sample, the IDBs will be placed in 1.5 mL sterile microcentrifuge tubes and stored at 4 °C until further analysis.

The BOIB [33] will be evaluated for the four interdental sites (15–16, 25–26, 35–36, and 45–46). This corresponds to the bleeding response to the horizontal pressure applied in the interdental space by a calibrated IDB. After 30 s, bleeding at each gingival unit will be recorded (0 = absence of bleeding after 30 s, and 1 = bleeding after 30 s). Then, interdental diameters and the BOIB will be evaluated for all other interdental sites.

Periodontal assessment, including first the GI and, second, the PI, will be performed. The dental plaque will be measured with the Löe and Silness plaque index, for which scores are as follows: 0 = no plaque, 1 = invisible plaque deposit but can be removed with a curette, 2 = plaque deposit covering the cervical 1/3, 3 = abundant plaque deposit (more than the cervical 1/3). Gingival inflammation will be evaluated with the Löe and Silness gingival index, the scores of which are as follows: 0 = healthy gingiva, 1 = erythematous gingiva not bleeding on probing, 2 = erythematous gingiva bleeding on probing, 3 = erythematous gingiva bleeding spontaneously.

PPD and CAL will be measured according to the criteria established by the consensus report of the 2017 World Workshop on the Classification of Periodontal and Peri-Implant Diseases and Conditions. These were based on stages defined by severity according to the level of interdental clinical attachment loss, and tooth loss, as well as the complexity, extent, and distribution, and incorporating a full mouth examination at six sites on each permanent tooth [34]. The initial stage should be determined using CAL.

Analysis of the interdental microbiota

Total DNA will be isolated from the interdental brushes using the QIAcube HT Plasticware and Cador Pathogen 96 QIAcube HT Kit (Qiagen, Hilden, Germany), according to the manufacturer’s guidelines. Quantitative real-time PCR will be carried out for total bacterial count and for 6 pathogens: Aggregatibacter actinomycetemcomitans, *Porphyromonas gingivalis*, Tannerella forsythia, Treponema denticola, Prevotella intermedia, and Fusobacterium nucleatum. 

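### As narrated, the plaque and gingival indices are scored after an interdental brush has entered every space, and the section's two statements of order conflict

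*Protocol article*

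**What the plan says.** Section 2.5.2 lists GI, PI and BOIB among the secondary outcomes, analysed as change from baseline. Section 2.6.2 describes the oral examination in this order.

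- At four premolar-molar spaces a conical probe gives the interdental diameter, a matching brush is chosen, and "the interdental biofilm will be removed using this sterile IDB".
- BOIB is recorded at the same four spaces: "This corresponds to the bleeding response to the horizontal pressure applied in the interdental space by a calibrated IDB".
- The rest of the mouth follows: "Then, interdental diameters and the BOIB will be evaluated for all other interdental sites".
- The next paragraph begins: "Periodontal assessment, including first the GI and, second, the PI, will be performed".

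The same section opens with a different order: "A clinical obstetric and oral examination, followed by interdental microbiota sampling, will be performed for all participants".

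Section 2.6.3 and Table 1 place the oral examination, including BOIB, at every visit. Interdental microbiota sampling is at T1, T4 and T6 only.

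**The concern.** PI grades the plaque that is present, and GI separates its upper grades by bleeding. An examination step that moves plaque or provokes bleeding should not come before the index it can alter unless there is a reason. Here a brush sized for the space precedes both indices.

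The intervention includes daily interdental brushing, so the proximal surfaces are where the arms should differ most in plaque. Controls would be expected to have more proximal plaque for the examiner's brush to take away. The PI comparison is therefore at risk of being weakened where it should be most informative. Scores taken after the disturbance cannot be restored by analysis.

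**Working it through.** The documents give no figure on this point. The check is a trace of the order, followed by an illustration on stated assumptions.

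**1. Order in the detailed text (Section 2.6.2).** Diameter and sampling at four sites, BOIB at those sites, diameter and BOIB at all other sites, GI, PI. By the time GI starts, a brush has been in every interdental space. Nowhere does the article place GI or PI before the brush.

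**2. What the article says the brush does.** Removal of biofilm is stated for the sampling step. On brush size: "The largest section of each colored band corresponds to the cleaning efficiency diameter of the respective brush". BOIB is described as pressure that elicits bleeding, read after 30 s. Some plaque removal during BOIB is plausible, but it is not stated.

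**3. What the indices read.**
- PI: "2 = plaque deposit covering the cervical 1/3, 3 = abundant plaque deposit (more than the cervical 1/3". Any plaque already displaced lowers the score.
- GI: "2 = erythematous gingiva bleeding on probing, 3 = erythematous gingiva bleeding spontaneously". Bleeding left over from BOIB can push a site to grade 2 or 3, so the expected shift in level is upward.

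**4. Conditions at the four index sites by visit (Table 1).**

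| Visit | Brush contact before GI and PI |
|---|---|
| T1 (baseline sample), T4, T6 | sampling pass plus BOIB |
| T2, T3, T5, T7 | BOIB only |

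Change from T1 therefore compares like with like at T4 and T6, but mixes conditions at T2, T3, T5 and T7.

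**5. The opening sentence taken as the order.** BOIB belongs to the oral examination in Table 1. If the whole examination comes first, the sample is taken from four spaces already brushed for BOIB, which disturbs the bacterial-load outcome. On that reading BOIB is still described before GI and PI.

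**6. Illustration of dilution (assumptions, not from the documents).** Let f be the share of scored surfaces that are proximal and r the fraction of proximal plaque removed, equal in both arms. Let D be the true PI difference, spread evenly over surfaces, and treat PI as proportional to plaque. The observed difference is

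(1 − f)·D + f·(1 − r)·D = (1 − f·r)·D.

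| f | r | Share of D kept, all surfaces |
|---|---|---|
| 1/2 | 0.25 | 1 − 0.125 = 0.875 |
| 1/2 | 0.75 | 1 − 0.375 = 0.625 |
| 2/3 | 0.25 | 1 − 0.167 = 0.833 |
| 2/3 | 0.75 | 1 − 0.500 = 0.500 |

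On proximal surfaces alone the share kept is 1 − r, which is 0.75 to 0.25 over the same range. PI is an ordinal 0 to 3 score, so proportionality is rough. The table shows only how the result depends on r, which nobody can read from the article. No comparable formula for GI can be filled in.

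**The case against.** **The order is inferred.** The sentence on GI and PI orders those two against each other; it does not say that they follow BOIB. It opens a new paragraph, and the article condenses a fuller protocol that may set out the steps. This stands as a limit on certainty. It does not remove the point: the text uses sequence words, offers no other place for GI and PI, and contradicts itself on where sampling falls.

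**Removal is stated only for sampling.** That is correct: four sites, at T1, T4 and T6. Elsewhere the loss of plaque rests on an assumption about BOIB. A reader might infer that the examiner cleans every proximal surface at every visit and so abolishes the PI contrast. The documents do not support this. They give no removal fraction, and the oral and lingual/palatal surfaces, which Section 2.10.3 also summarises, are not reached by an interdental brush.

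**GI.** A reader might infer that grade 3 can no longer be distinguished from bleeding caused by the brush. The text shows only that residual bleeding could be scored this way. Grade 2 is itself provoked bleeding.

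**Both arms are treated alike by examiners described as blinded.** This stands. The expected PI effect is dilution, so it is unlikely to manufacture a benefit. Blinding does not prevent dilution, however. GI distortion could also differ by arm if gums used to brushing bleed less.

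**Any order has a cost.** Scoring GI first means probing before BOIB, which can alter BOIB. Dropping the index sites would discard spaces that the article itself singles out as the most prone to inflammation. Both objections stand, and the change proposed below takes them into account.

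**Conclusion.** The point holds in a limited form. Followed as narrated, Section 2.6.2 scores two secondary outcomes after an interdental brush has been used for BOIB at all spaces at every visit, and additionally for sampling at four spaces at T1, T4 and T6. The likely consequence is some dilution of the PI contrast on proximal surfaces and some upward distortion of GI grades. Neither can be sized from the documents; the range above is an illustration only. Change from baseline at the index sites also mixes two measurement conditions, and the opening sentence of the section contradicts the detailed order.

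The conclusion assumes that the narrative order is the order of execution and that a BOIB insertion removes at least some plaque. It does not extend to the primary pre-eclampsia outcome or to the sample size, since neither uses these indices. The change is worth making because it is cheap and the loss is avoidable.

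**What to change.** State one examination order in Section 2.6.2, identical for both arms and applied at all visits.

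1. On sampling visits, take the microbiota sample at the four index sites first.
2. Score PI before any conical probe or interdental brush is inserted: at all sites on non-sampling visits, and at all sites other than the four index sites on sampling visits.
3. Fix and state the order of GI and BOIB, acknowledging that each can provoke bleeding, and keep it the same at every visit.
4. Rewrite the section's opening sentence to agree with this order.
5. Keep the four index sites in PI and GI, and add a sensitivity summary of both indices without them, because on sampling visits those sites are still scored after a brush pass.

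The cost is a revised examiner sequence, a calibration session that uses it, and one extra summary. No visits, equipment or participants are added.

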#### 2.6.3. Follow-Up Visits

Visits will be made according to the pregnant woman’s monthly follow-up schedule (Table 1). Obstetric clinical examination, biological analysis, and oral clinical examination will performed at each visit. Interdental sampling will be realized for all participants at 6 and 8 months of gestation. 

Participants in the intervention group will be asked about compliance with the study treatment (control of hygiene methods and techniques, and acceptance).

#### 2.6.4. Delivery Data Collection

Following delivery, clinical data will be collected from medical records: length of gestation, occurrence of PE, birth weight of the child, and fetal complications.

### 2.7. Sample Size

Reduction in PE will be considered the primary outcome variable, and an estimate of the mean difference in PE reduction will be used to calculate the sample size. The primary acceptance criterion will be the PE effect of the evaluated medical devices showing at least a moderate effect of 20%.

To show a reduction in PE from 20% to 12% (with alpha = 5%, beta = 80%), coefficient of intraclass correlation of 0.03 and in a unilateral proportion test, we initially calculated 440 subjects per group. Assuming a potential dropout rate of 10%, 880 participants were determined as the target for patient inclusion.

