#### 2.10.3. Statistical Methods

The final analysis of the data will be based on intention-to-treat and will be performed with the STATA MP 16.0 software (College Station, TX 77845, USA). All principal statistical analyses will be based on the clusters as allocated in the randomization [36]. Intention-to-treat analyses will be performed on the imputed data from all patients using multiple imputation by chained equations, based on a Monte Carlo–Markov chain algorithm under missing at random data hypothesis. Unilateral analysis to study the superiority of intervention over control group will be programmed. Data entry and preliminary checks for error and internal validity will be carried out at each study site, with corresponding statistical analyses conducted at a central level. A series of explanatory analyses will also be conducted in which clinics and/or individuals deviating from the protocol will be excluded. Additionally, per-protocol analysis using the same methodology as the intention-to-treat analyses will be performed based on participants with a complete set of outcome data at endpoint.

The main analytical technique used to assess the effect of intervention on the primary outcome will be an application of the Mantel–Haenszel test adapted to the cluster randomization design. Baseline tables will be created comparing the intervention groups with respect to both cluster-level and individual-level risk factors. 

Groups will be compared as at randomization. The primary endpoint will be estimated by the Kaplan–Meier method (survival analysis) and comparison of the different groups by the Log Rank test (*p* < 0.05). A multivariate analysis by a Cox regression model will be used to explore the relationship between the risk function associated with PE and the intervention after adjustment for site, amenorrhea at inclusion, gestational age, maternal age, and periodontal parameters at inclusion. Continuous outcome variables will be analyzed using mixed model regression, with the clinic status treated as a random effect. Analyses will also be conducted to explore the possibility of an interaction effect between intervention and clinic size. All statistical analyses performed will account for the within-clinic correlation that would invalidate the application of standard statistical methods. The results will be communicated according to CONSORT guidelines.

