Secondary analyses will also be performed comparing, as at randomization, the: (i) evolution of the pathogenic bacterial load of the interdental microbiota in the pregnant women intervention group compared to the control group, (ii) evolution of clinical signs of periodontal conditions in the pregnant women intervention group compared to the control group, and (iii) effect of individual oral prophylaxis during pregnancy on the risk of adverse perinatal outcomes. For dental clinical outcomes, mean and median values of clinical parameters for all oral, lingual/palatal, and proximal sites will be calculated per patient. Variations between the first and follow-up visits will be calculated.

Microbiological variables will be presented as total anaerobic counts, frequency of detection of target pathogens, counts of each pathogen studied, and proportions of each pathogen in the total microbiota. Total anaerobic counts will be log-transformed to match a normal distribution. 

The Shapiro–Wilk goodness-of-fit test and box plots will be used to determine the normal distribution of quantitative variables. Differences between groups at baseline and at follow-up visits will be determined by paired t-test or Mann–Whitney U tests for quantitative outcomes. In addition, clinical variables will be compared to repeated measures by ANOVA with Bonferroni post hoc correction controlling for visit for within-group comparisons, group (intervention or control) for between-group comparisons, and interaction between amenorrhea time and group. 

Results will be considered statistically significant at *p* < 0.05.

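### The stated inputs do not give 440 per group: 880 women in 16 clinics have about 64% power at one-sided 5%, not 80%, and the primary p < 0.05 carries no side

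*Protocol article*

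**What the plan says.** Protocol article, section 2.7 (Sample Size), takes pre-eclampsia rates of 20% and 12% and continues: "with alpha = 5%, beta = 80%), coefficient of intraclass correlation of 0.03 and in a unilateral proportion test, we initially calculated 440 subjects per group". It then assumes 10% dropout and sets the target at 880 women. Section 2.8 (Recruitment) divides these into 16 clinics of 55, and section 2.1 allocates clinics 1:1, so there are eight per arm.

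Section 2.10.3 (Statistical Methods) repeats the side: "Unilateral analysis to study the superiority of intervention over control group will be programmed". The main technique for the primary outcome is a Mantel–Haenszel test adapted to clusters, with neither side nor alpha given in that sentence. The primary endpoint is also analysed by survival methods, with "comparison of the different groups by the Log Rank test (*p* < 0.05" as the threshold. The section closes with a general rule: "Results will be considered statistically significant at *p* < 0.05". No side is attached to either threshold.

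**The concern.** Two things in the same chain looked wrong.

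- **The number.** Section 2.7 presents 440 as the result of listed inputs that include an intraclass correlation. If the inputs do not give 440, the reader is told the trial has 80% power when it has something else. As printed, beta = 80% would mean 20% power; it is evidently a slip for power.
- **The decision rule.** The plan says one-sided 5%, but the thresholds say only p < 0.05. Log-rank and Mantel–Haenszel tests are usually reported as chi-square tests with a two-sided p-value. A favourable result with a two-sided p between 0.05 and 0.10 passes under one reading and fails under the other.

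At stake are the stated power of the trial and the verdict on a borderline result. A trial with little more than even power is fairly likely to produce one.

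**Working it through.** **Inputs.** From section 2.7: p1 = 0.20, p2 = 0.12, one-sided alpha 5%, power 80% (written as beta), ICC 0.03, dropout 10%. From section 2.8: 16 clinics of 55.

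**1. Trying to reproduce 440.** The standard two-proportion formula is

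n = [z_α·√(2·p̄·q̄) + z_β·√(p1q1 + p2q2)]² / (p1 − p2)²

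with p̄ = 0.16, √(2·0.16·0.84) = 0.5185 and √(0.1600 + 0.1056) = 0.5154.

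- One-sided 5%, 80% power: (1.645·0.5185 + 0.8416·0.5154)² / 0.0064 = 258.6, so 259 per group (284 with continuity correction).
- Design effect at 55 per clinic: 1 + 54·0.03 = 2.62.
- Clustered: 259·2.62 = 678.6, so about 679 per group.
- With 10% dropout: 259·2.62/0.9 = 754 per group.

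None of these is 440. At 55 per clinic, 679 means 679/55 = 12.3, that is 13 clinics per arm, against eight planned.

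**2. Dropout.** 2·440 = 880, so the target after dropout equals the figure before it. Adding 10% would give 440/0.9 = 489 per group.

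**3. Power of what is planned.** Effective size per arm is 440/2.62 = 167.9, and power = Φ[(0.08·√n_eff − z_α·0.5185)/0.5154].

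| Setting | one-sided 5% | two-sided 5% |
|---|---|---|
| 440 per arm, clustering ignored | 94.5% | 90.0% |
| 440 per arm, design effect 2.62 | 63.9% | 51.6% |
| 396 per arm after 10% dropout (49.5 per clinic, design effect 2.455) | 62.4% | 50.0% |
| 440 per arm, design effect 2.62, t on 14 df | 60.6% | 46.5% |

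**4. Routes that do reach 440.**

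- Two-sided 5%, 90% power, no clustering, no dropout: 439.2, so 440.
- Two-sided 5%, 85% power, continuity correction: 400.1; times 1.1 for dropout gives 440.2.
- The stated one-sided 5% and 80% with ICC 0.03: 440/258.6 = 1.70 as design effect, which is about 24 women per clinic.

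**5. The side of the threshold.** One-sided 5% requires z > 1.645; p < 0.05 read as two-sided requires z > 1.96. Under the planned effect the chance of landing between them is 63.9% − 51.6%, about 12%. With a control rate of 20% and the effective size above, the smallest reduction declared significant is about 6.7 points one-sided and 7.9 points two-sided (7.1 and 8.5 with t on 14 df). The chance of wrongly claiming benefit is 5% or 2.5%.

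**The case against.** The strongest reply concerns the side. The plan says unilateral in both the sizing and the analysis, no sentence states a two-sided primary test, and p < 0.05 is numerically the same as one-sided 5%. A one-degree-of-freedom test can be reported one-sided through its signed root. The closing rule in section 2.10.3 follows paragraphs on secondary, dental and microbiological analyses and may be generic. This largely stands: the side is a labelling ambiguity, not a contradiction.

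A reader might infer more from the number itself: because 440 equals the two-sided 5%, 90% power, unclustered figure, the trial was really sized two-sided and should be tested that way. The document does not support this. That match changes three stated inputs at once (side, power, ICC). Other input sets also reach 440, and one of them keeps the stated side, power and ICC and changes only the clinic size. The coincidence does not show how 440 was obtained, so it would be wrong to record those inputs as the ones used or to treat one-sided 5% as an error. Moving to two-sided 5% is a preference.

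This reply does not rescue the number. Section 2.7 gives no clinic size, but section 2.8 fixes 55, and at 55 the stated inputs do not give 440.

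**Conclusion.** The point holds in two parts of unequal weight.

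The main part is arithmetic: 440 per group does not follow from the inputs printed beside it. They need 259 per group without clustering and about 679 with it. The planned 880 women give about 64% power at the stated one-sided 5%, about 62% after dropout, instead of 80%. At two-sided 5% the figures are about 52% and 50%. This assumes ICC 0.03 as stated, equal clinics of 55, a normal approximation, and beta = 80% read as 80% power. Using t on 14 degrees of freedom lowers the power further. The dropout figures treat lost women as lost information; the planned multiple imputation could recover some of it.

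The lesser part is that the primary threshold has no side. About 12% of trials under the planned effect would be decided by the reading chosen. The document already points to one-sided, so this is a matter of labelling.

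**What to change.** **Section 2.7.** Write power = 80% where beta = 80% stands. Stop presenting 440 as the product of the listed inputs, or give the inputs that did produce it if the sponsor's records show them. Restate the power of the fixed 880 women with ICC 0.03, 55 per clinic and 10% dropout at the chosen alpha: about 62% at one-sided 5%, about 50% at two-sided 5%.

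**Section 2.10.3.** Attach the side to the primary-test threshold, at both the Mantel–Haenszel and the log-rank sentence. Either rule will do:

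- one-sided p < 0.05 in favour of the intervention, with a two-sided 90% confidence interval, which is what the plan now states; or
- two-sided p < 0.05 with a 95% confidence interval, if the sponsor prefers it.

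Say whether the general p < 0.05 rule is meant for the other analyses only, and with which side.

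**Cost.** Wording only, to be settled before unblinding, and no extra patients. The price is a less favourable stated power; choosing two-sided 5% lowers it by about 12 further points. If the sponsor wants 80% power instead, that is a design change: at 55 per clinic it needs more clinics.
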